**Table 4. CFHealthHub data (research arm only)**

|                                                                                                 | Completed by?          | Baseline (intervention) visit | At intervention visit s with interventionist | Between sessions | At clinic visits | 5 months (+/- 1 month) from consent visit | Up till 30th April 2017 |
|-------------------------------------------------------------------------------------------------|------------------------|-------------------------------|----------------------------------------------|------------------|------------------|-------------------------------------------|-------------------------|
| Clinician metrics                                                                        |                        |                               |                                              |                  |                  |                                           |                         |
| Adherence data*                                                                                 | PWCF                   | ●                             | ●                                            | ●                | ●                | ●                                         | ●                       |
| Recommendation of modules by interventionist                                                    | Interventionist        | ●                             | ●                                            | -                | ●                | -                                         | x                       |
| Feed back to participant their adherence data screens (data click)                              | Interventionist        | ●                             | ●                                            | -                | ●                | -                                         | x                       |
| Check prescription with participant                                                             | Interventionist        | ●                             | ●                                            | -                | ●                | -                                         | x                       |
| Order of clicks                                                                                 | CFHH                   | ●                             | ●                                            | -                | ●                | -                                         | x                       |
| Interventionist responds to patient changing prescription                                       | Interventionist        | -                             | ●                                            | ●                | ●                | ●                                         | x                       |
| Monthly check on prescription +                                                                 | Interventionist / CTRU | ●                             | ●                                            | ●                | ●                | ●                                         | x                       |
| Time in and out preparation                                                                     | Interventionist /CFHH  | ●                             | ●                                            | -                | -                | ●                                         | x                       |
| Time in and out with patient                                                                    | Interventionist /CFHH  | ●                             | ●                                            | -                | -                | ●                                         | x                       |
| Time in and out review                                                                          | Interventionist /CFHH  | ●                             | ●                                            | -                | -                | ●                                         | x                       |
| Patient metrics                                                                          |                        |                               |                                              |                  |                  |                                           |                         |
| Adherence (number of nebulized doses taken per day.)                                | PWCF                   | ●                             | ●                                            | ●                | ●                | ●                                         | x                       |
| Duration of inhalation                                                                          | Nebuliser              | ●                             | ●                                            | -                | -                | -                                         | x                       |
| Accessing CFHealthHub – look at adherence data                                                  | PWCF                   | ●                             | ●                                            | -                | -                | -                                         | x                       |
| Accessing CFHealthHub – look at ‘My Toolkit’                                                    | PWCF                   | ●                             | ●                                            | -                | -                | -                                         | x                       |
| Accessing CFHealthHub problem solving / education / talking heads pages outside of ‘My Toolkit’ | PWCF                   | ●                             | ●                                            | -                | -                | -                                         | x                       |
| Accessing CF HealthHub – first to last click in a session                                       | PWCF                   | ●                             | ●                                            | -                | -                | -                                         | x                       |

\*Adherence data collected for both research and control arms

+ Monthly prescription checked by CTRU centrally to alert local interventionists to any potential changes in control arm and potentially also intervention arm

X data continued to be collected in CFHealthHub and interventionist responds for those participants who have “opted in” to receive intervention till 30/4/17

To be broken down in statistical analysis plan.

**Figure 6. Participant timeline for the external pilot RCT**[figure not shown]

\*When I-nebs are converted to Bi-nebs a representative from the company (Philips) will do this between the consent visit and first intervention visit.

The study recognises that flexibility in accommodating participant schedules may cause time windows to change but this will allow us to adapt the intervention for the main RCT.

## 8. Sampling

### 8.1 Quantitative components

#### 8.1.1 Sites

Two large specialist CF centres have been screened for their ability to recruit participants based on the number of participants they have on their CF registry and their motivation to participate in the pilot trial.

#### 8.1.2 Sample size

The sample size for a feasibility study should be adequate to estimate the uncertain critical parameters (standard deviations for continuous outcomes; consent rates, event rates, attrition rates for binary outcomes) needed to inform the design of the full RCT with sufficient precision [37, 58–60]. For the main RCT, the target sample size is 688 participants (344 per arm). We are proposing that 15 CF units recruit on average 46 patients in six months, a recruitment rate of approximately eight patients per centre per month.

To assess whether this recruitment rate is feasible the external pilot RCT will open in two CF units for 12 months, with four months recruitment, one months 'run-in' period (the period between the consent and baseline visit), and 5 (+/-1) months follow up. To match the proposed recruitment rate of the main RCT, the target sample over the four months for which the pilot RCT is open, will be 32 per centre (64 in total from the two pilot centres). We propose to recruit to time, that is for a fixed period of four months rather than to a fixed sample size. We would want to see a minimum of 75% of the recruitment target to be confident of the trial viability i.e. at least 48 patients in total consented and randomized in four months' of recruitment from two centres.

#### 8.1.3 Approach, non-participation and recruitment

**Approach:** Health professionals involved in approaching and screening PWCF and collecting data will be trained in the study protocol and procedures. Additionally those taking consent will have up-to-date training in Good Clinical Practice (GCP). All study personnel will be named on the study delegation log. Health professionals working with the CF team will identify a sample of PWCF registered at the centre via the CF registry database locally. All inclusion and exclusion criteria will be assessable via patient records and they will exclude any patients who do not fit the eligibility criteria.

A member of the participant's direct clinical team will send the potential participant a PIS and introductory letter by post or give the written information during a routine clinic visit. A sticker with a website address and Quick Response code will be placed in the envelope both of which will link to a video of the researcher explaining the study. If information is provided in a routine clinic visit, the clinical care team will seek permission for the ACTiF Interventionist to follow up with a phone call in order to answer any further questions and discuss involvement. Written informed consent may be conducted at this visit where the participant is happy to take part as this is a low risk trial.

**Telephone call:** Up to a week after posting out the information, the ACTiF Interventionist will telephone the PWCF to discuss the study over the phone and answer any questions. If the potential participant is happy to take part, the ACTiF Interventionist will arrange an appointment to gather written informed consent.

**Non-participation:** Spontaneously offered reasons for non-participation in the trial will be recorded.

## 8.2 Qualitative components

At each of the two pilot sites we will undertake:

- Audio-recordings of all 16 initial assessments for PWCF in the intervention arm and 10-12 consultations between the senior interventionist from the MDT (or other MDT member) and PWCF in the control arm. Numbers will depend on numbers of PWCF giving written consent for this.
- 10-12 semi-structured face-to-face (or telephone or skype) interviews with PWCF receiving the intervention and 10-12 semi-structured face-to-face interviews with PWCF in the control arm (total n~40-48 PWCF; n~40-48 interviews);
- two semi-structured face-to-face (or telephone or skype) interviews with each of the two interventionists in each centre (total n=4 interventionists; n=8 interviews); and,
- two semi-structured (face to face, telephone or skype) interviews with two members of the MDT (total n=4 staff; n=8 interviews).

Written informed consent will be obtained from both the interventionist and the PWCF participating in the audio recording when they consent to be in the study. Separate consent will be sought from PWCF and interventionists or members of the wider CF team for semi-structured interviews.

## 9. Assignment of interventions

### 9.1 Sequence generation

Participants will be allocated in equal proportions to one of the two groups using a computer generated pseudo-random list, stratified by centre and the number of days participants have been on IV antibiotics in the previous 12 month period as collected at consent visit, with random permuted blocks of varying sizes. The two categories for stratification within the number of IV days will be (i) less than or equal to 14 days and (ii) greater than 14 days.

### 9.2 Allocation concealment

The allocation sequence will be hosted by the Sheffield CTRU in accordance with their standard operating procedures and will be held on a secure server. Access to the allocation sequence will be restricted to those with authorisation. The sequence will be concealed until recruitment, data collection, and analyses are complete.

### 9.3 Implementation

The allocation sequence will be created by a Sheffield CTRU statistician who is not otherwise associated with the trial. At the consent visit, a health professional who is named on the delegation log, will go over the patient information sheet again with the study candidate and answer any questions. If the PWCF is still willing to enter the trial, they obtain full written consent and complete the eligibility form. If the participant is eligible, then baseline assessments will be taken. The recruiting health professional will log into the remote, secure Internet-based randomisation system and enter basic demographic information, after which the allocation will be revealed.

### 9.4 Blinding

After revelation of the allocation, only the statisticians will be blinded to allocation as per CTRU SOPs (ST001 and ST005)

## 10. Data collection, management and analysis

### 10.1 Quantitative data

#### 10.1.1 Data collection methods

**Data handling and record keeping.** The Sheffield CTRU will oversee data collection, management and analysis and ensure the trial is undertaken according to Good Clinical Practice Guidelines and CTRU standard operating procedures. Data will be collected and retained in accordance with the Data Protection Act 1998. Patients will be reassured that all data which are collected during the course of the research will be kept strictly confidential.

The study team will train those collecting data in the study procedures before the trial begins. Data will either be collected directly from the participants, carers, interventionist, CFHealthHub or from source documents (e.g. patient notes) and input onto the CRF or Sheffield CTRU's electronic web-based data capture system (Prospect). The Data Monitoring and Management Plan for the study will provide further guidance on the types and levels of data and how these will be monitored and verified. Some essential documents may be posted to the central team to facilitate this e.g. participant consent forms in which case this will be detailed in the appropriate participant PIS and consent forms.

The CTRU will perform checks with the participant via monthly phone calls to ensure data is being captured and alert the local interventionist if there is an indication of a prescription change and a need to check pseudomonas (or other microorganism) status. This is required for the correct denominator to assess "normative adherence". Data will be extracted from the CF registry to understand exacerbations in the preceding 12 months since prior exacerbations can have a bearing on the optimum target regimen.

#### ***Plans to promote participant retention and complete follow-up.***

Participant retention will be ensured by the following procedure:

1. At each point of contact, the interventionist will check with the participant that the Qualcomm hub or Smartphone hub is plugged in and turned on. A member of CTRU who is performing data and prescription checks may alert the interventionist. They will remind the participant of the proximity required for data transfer (10 metres)
2. In the event of no data being displayed in CFHealthHub for a period of at least a week (and the participant is not known to be on holiday) the interventionist will make contact with the participant (Email/Text/Telephone call) to check that the following
  - That the Qualcomm or Smartphone hub is plugged in
  - That the Qualcomm hub is working (showing solid green and yellow lights on the display)
  - That they have been within range of the Qualcomm hub sufficient to facilitate data transfer (10 metres)
  - That the Smartphone hub is switched on (showing the locked 'password' screen when any button is pressed)
  - That the Bi-neb and Smartphone hub have been kept in the same room, or at least have been in close proximity at some point during the day.

Any participants using the Bi-neb who are still experiencing issues after following the steps above, may receive a face to face or telephone support (at home or hospital) from the clinical trainer to resolve any outstanding issues.

#### ***Troubleshooting:***

Data capture will be monitored both by interventionist at the site and centrally by the CTRU. In the event of data not being uploaded patients will be contacted to trouble shoot problems. Patients will be offered support to suit their circumstances including home visits (conducted by the members of the site research team) where necessary.

### 10.1.2 Data Management

Anonymised trial data will be entered onto a validated database system designed to an agreed specification between the Chief Investigator and Sheffield CTRU. The research staff at sites (mainly the ACTiF interventionist) will be responsible for data entry locally. The Sheffield CTRU Trial Manager, research assistant and the Data Management Team will work with sites to ensure the quality of data provided. The study manager, research assistant, data manager, PI's, any research nurses and site interventionist will have access to the anonymised data on the database through the use of usernames and encrypted passwords. The system has a full electronic audit trail and will be regularly backed up. The secure data management system will incorporate quality control procedures to validate the study data. Error reports will be generated where data clarification is needed. Output for analysis will be generated in a format and at intervals to be agreed between Sheffield CTRU and the Chief Investigator.

Trial documents will be retained in a secure location during and after the trial has finished. The study will use the CTRU's in-house data management system (Prospect) for the capture and storage of participant data. Prospect stores all data in a PostgreSQL database on virtual servers hosted by Corporate Information and Computing Services (CiCS) at the University of Sheffield. Prospect uses industry standard techniques to provide security, including password authentication and encryption using SSL/TLS. Access to Prospect is controlled by usernames and encrypted passwords, and a comprehensive privilege management feature can be used to ensure that users have access to only the minimum amount of data required to complete their tasks. This can be used to restrict access to personal identifiable data.

Participants who give consent to the qualitative part of this study will also give consent to their name and address to be given to the University of Sheffield qualitative research staff in order to be contactable.

### 10.1.3 Data quality assurance

Prospect provides a full electronic audit trail, as well as validation and verification features which will be used to monitor study data quality, in line with CTRU SOPs and the Data Management Plan (DMP). Error reports will be generated where data clarification is required. Rates of missing data and data points which are out of the expected or allowed range will be presented to the team at monthly management group meetings.

## 10.2 Qualitative data

### 10.2.1 Audio recordings of consultations

All initial assessments will be audio recorded with permission (n=16 in each site). Findings from early assessments will be fed back to the interventionist so that changes can be made to the intervention delivery before subsequent assessments. Consultations between the senior interventionist and PWCF in the control arm will be audio recorded with permission (n=10-12 in each site). Encrypted digital recorders will be used and recordings sent securely to the research team for analysis.

### 10.2.2 Semi-structured interviews: participants

In each site we will interview 3-4 PWCF receiving the intervention who are recruited at the beginning of the pilot. We will interview them around one month into the intervention to seek views of the most intensive part of the intervention. This will identify any problems early and be fed back to the intervention development team, staff delivering the intervention, and trial staff. We will interview 5-6 PWCF around four to six months into the intervention. These PWCF will have experienced more independent use of the CFHealthHub and we can explore how to keep PWCF engaged with the intervention in the longer term. We will interview 2-3 PWCF who drop out of the intervention to explore why this occurred. We will interview 10-12 PWCF in the control arm around four to six months into the trial to explore whether they have experienced aspects of patient activation and leakage of the intervention.

### 10.2.3 Semi-structured interviews: professionals

The first interviews with the interventionist and senior interventionist in each site will take place after they have undertaken assessments with the first few PWCF to identify teething problems with the intervention or the trial and the comprehensiveness of the training sessions they received. The findings will be fed back to the team to consider whether changes are needed to the intervention or trial protocol. The second interviews will take place when the first few PWCF have completed the intervention to allow the interventionist to reflect back over the whole process. The interventionists may have different lengths of experience of working with CF, nebulisers or behaviour change and we will consider the influence of differences in backgrounds on their ability to implement the intervention.

We will also undertake interviews with two members of the MDT at each centre when the first few PWCF have received 2-3 months of the intervention and then again towards the end of the feasibility study when all PWCF have been recruited and received around 3 months of the intervention.

### 10.2.4 Undertaking the interviews

For the interviews we have developed topic guides based on our research questions and these are attached to the application. Topic guides develop throughout any qualitative interview study and our topic guides may change as the study progresses. We will audio record all interviews after receiving written permission to do so. We will use an encrypted digital recorder. Reflexive notes will be made during and after the interviews. We expect

interviews to last around one hour. We do not expect data saturation in pilot studies; the aim is to identify any learning that can be addressed in preparation for the full trial.

## 11. Data analysis

### 11.1 Quantitative analysis

The analysis will be performed after data lock by a CTRU statistician under the supervision of the senior study statistician. As the trial is a pragmatic parallel group RCT data will be reported and presented according to the CONSORT 2010 statement [61] with reference to proposed extension for pilot / feasibility studies [37]. As a pilot/feasibility study the main analysis will be mainly descriptive and focus on confidence interval estimation and not formal hypothesis testing [58]. We will report rates of consent, recruitment and follow-up by centre and by randomized group.

Clinical outcome measures will be summarised overall and by randomized group. Baseline demographic (age, gender), physical measurements (e.g. weight, height, BMI), and patient reported outcome measures (EQ-5D, PAM-13, Assessment of Routine, MAD-3, SRBAI, CFQ-R, GAD-7, COM-BMQ, PHQ-8), and clinical measurements (e.g. FEV1, IV days in last registry year ) will be described and summarised overall and for both treatment groups.

The primary outcome is the number of pulmonary exacerbations treated with IV antibiotics over the 6 month post-randomisation follow-up period. We will also include, as part of the feasibility analysis, estimation of the effect size for the 6-month pulmonary exacerbations outcome with 95% confidence interval estimates to check that the likely effect is within a clinically relevant range (as confirmation that it is worth progressing with the full trial). For this we will use a Poisson generalised linear model (GLM). Secondary continuous outcomes such as six-month post randomisation FEV1, BMI EQ-5D, PAM-13, Assessment of Routine, MAD-3, SRBAI, CFQ-R, GAD-7, COM-BMQ, PHQ-8) will be analysed with a multiple linear regression model with the baseline value of the outcome and randomised group as covariates. The treatment group coefficient and its associated 95% confidence interval will be reported from the various multiple linear regression models. The mean level of adherence (to prescribed medication) between the intervention and control groups over the 6 month post-randomisation follow-up period will also be reported and compared between the groups and a 95% confidence interval (CI) for the mean difference in this parameter between the randomised groups will also be calculated.

Further analyses with the objective nebuliser data will be performed to explore the process of habit formation with the delivery of the adherence intervention. The analyses will include:

- (a) generating objective habit scores by taking into account time of nebuliser use
- (b) using statistical process control to identify when periods of stability is achieved
- (c) other time-series methods, including cross-correlation between habit scores and adherence.

Adverse events will be based on serious adverse events (SAE) case report forms. A serious adverse event is defined as any adverse event or adverse reaction that results in death, is life-threatening, requires hospitalisation or prolongation of existing hospitalisation, results in persistent or significant disability or incapacity, or is a congenital anomaly or birth defect.

The following summaries will be presented as overall rates and stratified by AE classification:

- the number and percentages of patients reported as having Serious Adverse Events (SAE) in each treatment arm; and,
- the number and percentages recorded as having all forms of Adverse Events (AE) in each arm.

This information along with the acceptability of the study design and protocol to patients/GPs; the safety of the intervention; patient recruitment and attrition/retention rates will enable us to determine whether or not the definitive RCT is feasible within a satisfactory timescale and cost envelope using UK centres alone.

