| Confirmation of eligibility form                                                                                                                                                                                                                                                                                                                                                                              | Prospect | Site          | ●             | -                             | -                | -                     | -                                         | -                                 |
| Informed consent                                                                                                                                                                                                                                                                                                                                                                                              | Prospect | Site          | ●             | -                             | -                | -                     | -                                         | -                                 |
| Intravenous days in last registry year                                                                                                                                                                                                                                                                                                                                                                        | Prospect | Site          | ●             | -                             | -                | -                     | -                                         | -                                 |
| Pseudomonas status +                                                                                                                                                                                                                                                                                                                                                                                          | Prospect | Site          | ●             | -                             | -                | -                     | -                                         | -                                 |

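### The primary exacerbation model names no baseline covariate, although prior-year exacerbations are already extracted and the listed secondary outcomes are baseline-adjusted

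*Protocol*

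**What the plan says.** Protocol section 11.1 defines the outcome: "The primary outcome is the number of pulmonary exacerbations treated with IV antibiotics over the 6 month post-randomisation follow-up period". The planned effect estimate comes with "95% confidence interval estimates to check that the likely effect is within a clinically relevant range", and the protocol treats this as support for going on to the full trial. The method is one sentence: "For this we will use a Poisson generalised linear model (GLM"). No covariate, stratification factor or method for the standard error is named.

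The following sentence is more specific about the listed secondary continuous outcomes (FEV1, BMI and the questionnaires), which get a "multiple linear regression model with the baseline value of the outcome and randomised group as covariates".

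The history of the primary outcome is collected. Section 10.1.1 states: "Data will be extracted from the CF registry to understand exacerbations in the preceding 12 months". The use given there is the target regimen for normative adherence, not the outcome model. Table 3 records "Intravenous days in last registry year" at the consent visit, and section 11.1 lists this item only for baseline description. Section 5.2.1 makes registry data an entry requirement. Section 9.1 stratifies randomisation by centre and by IV days in the previous 12 months, cut at 14 days.

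**The concern.** Prior-year exacerbations are the nearest available baseline for the primary outcome, and the design already treats IV history as prognostic by stratifying on it. Yet within one paragraph the protocol fixes a baseline covariate for lesser outcomes and none for the primary count.

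The two-level IV-day stratifier does not separate people within the upper band, where frequent exacerbators sit and where a large share of events may arise. With 64 participants, or the minimum of 48, a few such people falling by chance in one arm can move the rate ratio. This estimate is meant to inform whether the full trial is worth running, and section 8.1.2 expects the pilot to supply uncertain design parameters for it. At stake are the precision of that estimate, the honesty of its interval, and the dispersion figure carried into planning.

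**Working it through.** **Plan's own figures.** Section 8.1.2: 2 centres × 4 months × 8 per month = 64; 0.75 × 64 = 48. Both reproduce. The protocol gives no event rate, rate ratio, dispersion or interval width for exacerbations.

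**Assumed inputs.** Section 2.1 gives 171,907 IV days in 2012 among about 10,000 people: 171,907 / 10,000 = 17.2 days per person-year. At an assumed 14 days per course, 17.2 / 14 = 1.2 courses a year, or about 0.6 per 6 months. The check therefore took control means of 0.5, 0.75 and 1.0 per 6 months. It used 1:1 allocation, a rate ratio of 0.8, and gamma frailty variance φ of 0, 0.5 and 1.0, shared by the prior and follow-up counts. φ = 0 means no overdispersion.

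**Step 1: what a plain Poisson GLM reports.** With dispersion fixed at 1, Var(log RR) ≈ 1/E0 + 1/E1, where E is expected events per arm. For 32 per arm and control mean 1.0, E0 = 32 and E1 = 25.6. The variance is 0.0313 + 0.0391 = 0.0703 and the SE 0.265. A prognostic covariate does not enter this formula.

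**Step 2: what the true variability is.** With frailty, Var(log RR) ≈ (1/μ0 + φ)/n0 + (1/μ1 + φ)/n1. For φ = 1.0: (1 + 1)/32 + (1.25 + 1)/32 = 0.0625 + 0.0703 = 0.1328, SE 0.364. A nominal 95% Poisson interval then covers about 2Φ(1.96 × 0.265/0.364) − 1 = 85%. Here the stated interval is too narrow, not too wide.

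**Step 3: effect of adding the prior count.** Simulation with 1,000 replicates per scenario, group alone against group + log(prior 12-month count + 0.5). Results for n = 64, unadjusted → adjusted:

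| Control mean | φ | Poisson SE | Dispersion-scaled SE | True SD | Coverage of plain Poisson interval |
|---|---|---|---|---|---|
| 0.5 | 0 | 0.388 → 0.391 | 0.388 → 0.391 | 0.394 → 0.395 | 96.4% → 96.3% |
| 0.5 | 0.5 | 0.391 → 0.395 | 0.425 → 0.418 | 0.441 → 0.433 | 94.1% → 94.5% |
| 0.5 | 1.0 | 0.393 → 0.398 | 0.458 → 0.432 | 0.480 → 0.456 | 90.7% → 92.5% |
| 0.75 | 0 | 0.314 → 0.316 | 0.313 → 0.315 | 0.333 → 0.336 | 94.8% → 94.5% |
| 0.75 | 0.5 | 0.316 → 0.319 | 0.359 → 0.344 | 0.379 → 0.356 | 90.1% → 92.4% |
| 0.75 | 1.0 | 0.317 → 0.322 | 0.402 → 0.359 | 0.423 → 0.380 | 87.6% → 91.9% |
| 1.0 | 0 | 0.270 → 0.272 | 0.268 → 0.270 | 0.284 → 0.287 | 93.9% → 94.0% |
| 1.0 | 0.5 | 0.272 → 0.274 | 0.324 → 0.304 | 0.324 → 0.298 | 91.2% → 92.9% |
| 1.0 | 1.0 | 0.272 → 0.276 | 0.364 → 0.312 | 0.369 → 0.308 | 85.3% → 91.9% |

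The simulated values in the last row agree with steps 1 and 2.

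- True SD: about 2-8% lower at φ = 0.5 and 5-17% lower at φ = 1.0. There is no gain at φ = 0.
- Plain Poisson SE: adjusted/unadjusted ratio 1.008-1.018 in all 18 scenarios (n = 48 and 64), so the interval widens by 1-2%.
- Dispersion-scaled SE: ratio 0.98-0.94 at φ = 0.5 and 0.95-0.86 at φ = 1.0. Only here does the interval shorten.

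**Step 4: other assumptions.** A second simulation at N = 64 (0.6-1.0 events per 6 months, frailty variance 0.5-2) gave a reduction in true SD of about 0-17%. Plain Poisson coverage rose, for example, from 87% to 93% and from 78% to 85%.

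**Step 5: gain over the stratifier.** With prior/follow-up correlation 0.23-0.50, frailty variance 1-2 and a dispersion-scaled SE, adding the count to a model that already held the binary IV-day stratifier cut the SE by a further 0-6%.

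**The case against.** The strongest objection is that a GLM's covariate list is ordinary SAP content. Section 11.1 does not say the model is unadjusted, and the SAP, which is not at hand, may name covariates. That stands as a limit: a reader might infer that the plan rules the prior count out, and silence does not support that. It is answered in part by the paragraph itself, which settles the same question for the listed secondary outcomes.

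A reader might also infer that leaving out the covariate makes the reported interval wider than it need be. For the model named this is wrong: steps 1 and 3 show that its interval widens slightly on adjustment, and with overdispersion it was too narrow to begin with. The linear-model rule that variance falls by the squared correlation does not describe a Poisson SE.

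Nor is every secondary continuous outcome baseline-adjusted. For adherence, section 11.1 says only that "a 95% confidence interval (CI) for the mean difference in this parameter between the randomised groups will also be calculated", with no baseline term.

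Gains in power are not a suitable measure either, since the analysis will "focus on confidence interval estimation and not formal hypothesis testing". The stop-go criteria in section 7.1 do not depend on this interval.

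Finally, section 10.1.1 does not say that the registry data are a count under the Fuchs definition used for the outcome, and the entry criterion requires registry data, not a complete 12-month count. The covariate is thus a close proxy for a baseline rather than a guaranteed identical measure. It can still be prognostic.

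**Conclusion.** The point holds as a better method that is available at almost no cost, not as an error that invalidates the analysis. Section 11.1 names a baseline covariate for the listed secondary continuous outcomes and none for the primary count, while relevant history is already collected.

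Under assumed overdispersion, adjustment lowers the true SD of the log rate ratio by roughly 0-17% at N = 64 and moves plain Poisson coverage towards 95%, without fully restoring it where frailty is large. The benefit is modest (0-6% on the SE) once the IV-day stratifier is included, and absent without overdispersion. A shorter printed interval also needs a standard error that allows for overdispersion. Event rates, frailty and the link between prior and follow-up counts are all assumptions. Step 3 lets both counts share one frailty, which favours adjustment; a weaker link would give less.

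**What to change.** In section 11.1, or in the SAP if it is silent, state that the exacerbation model includes randomised group, the two stratification factors and the prior-12-month exacerbation count, for example as log(count + 1). State that the standard error is dispersion-scaled or robust; without this the covariate will not shorten the interval. Report the dispersion with and without the prior count, so that the main RCT can be planned for an adjusted analysis.

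Say in advance what happens if registry counts prove incomplete: use IV days in the last registry year as the covariate for all participants, rather than mixing two measures in one variable. Fixing this before data lock also removes a choice of covariates made after seeing the results.

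Cost: one sentence and no new data collection. The prior count adds one parameter with about 48-64 participants. Events may be few: at a control mean of 0.5 and a rate ratio of 0.8, 64 participants yield 16 + 12.8 = 28.8 expected events. The covariate list should therefore stop there.
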